|----------------------------------------|---------------------------------------------------------------------------------------------------------------------------------------------------------------------------------------------------------------------------------------------------------------------------------------------------------------------------------------------------------------------------------------------------------------------|
|                                        | 
Primary safety endpoint
 
 
1. Number and occurrence of related SAE and Grade 3 AE from time of first administration of ivermectin until the end of the study
 
 
Secondary safety endpoint
 
 
1. Number and occurrence of any AE from time of first administration of ivermectin until the end of the study
 
 |
| Data and Safety Monitoring Plan | Participants will be treated when criteria to initiate a rescue treatment are reached or at the end of the active study follow-up period (D7).                                                                                                                                                                                                                                                                      |

## 2. Abbreviations

|      |                                           |
|------|-------------------------------------------|
| AE   | Adverse Event                             |
| ALT  | Alanine aminotransferase                  |
| AST  | Aspartate transaminase                    |
| CBC  | Complete Blood Count                      |
| CRP  | C Reactive Protein                        |
| DSMB | Data and Safety Monitoring Board          |
| EC   | Ethics Committee                          |
| GCP  | Good Clinical Practice                    |
| GGT  | Gamma-Glutamyl Transpeptidase             |
| HIV  | Human Immunodeficiency Virus              |
| ICH  | International Conference on Harmonisation |

### **3. Background and Rationale**

#### **3.1. Epidemiology and consequences of malaria**

In spite of remarkable progress over the last 15 years (1), malaria continues to be a major public health problem in the developing world with an estimated 219 million cases and 435.000 deaths in 2017 (2), an incidence that has levelled off over the last years. The enormous economic and social consequences of malaria have been well documented (3). By far the major burden is in Africa and the enormous economic and social consequences of malaria have been well documented (3).

#### **3.2. Endectocides and ivermectin**

Ivermectin is an anti-parasitic medicine approved for the treatment and control of human onchocerciasis, lymphatic filariasis, strongyloidiasis and scabies (4). It is also an endectocide, a systemic insecticide capable of killing mosquitoes that feed on treated participants regardless of the time and place of biting (5). Ivermectin mass drug administration could circumvent residual transmission and potentially become a complementary tool for malaria elimination. One key issue is the classification of this potential endectocide-based intervention. Many policy-makers consider it as an altruistic intervention in which the main benefit from exposing an individual to the drug is experienced at community level once mosquitoes die. Other authors consider a reduction in local transmission as a personal benefit that warrants mass treatment. In the case of ivermectin, additional personal benefits are expected from its effects on helminths and ectoparasites (6). Within the current study the activity of ivermectin against the blood stage parasite of *P. falciparum* will be investigated, this would present an additional benefit for the individual person in case ivermectin will be widely used for malaria transmission blocking. In addition, ivermectin shall have a different mechanism of action than other antimalarials and therefore constitute a particularly interesting combination partner for malaria treatments, especially for use in malaria control and elimination settings as well as programs targeting co-infections.

#### **3.3. Safety profile of ivermectin**

Ivermectin has been licensed for human use for almost 30 years, and its safety has been assessed in over 70 trials. More than 2.7 billion 150-200 mcg/kg single doses have been distributed through the Mectizan Donation program (7). In individuals with a high *Loa loa* microfilarial load, Ivermectin can cause severe encephalopathy (6). Outside *Loa loa* endemic areas, the drug is remarkably safe. In onchocerciasis-infected patients, adverse events (AE) to ivermectin are

usually mild, transient, associated with intensity of microfilarial infection and primarily characterized as mild Mazzoti-type reactions to dying microfilaria (8). These effects wane in subsequent administrations (9). No significant dose-response has been found between ivermectin plasma levels and AEs in human dose-ranging studies (10). A recent Cochrane review of ivermectin for river blindness shows that side effects are rarely reported (11). The French authorities recommend up to 400 µg/kg for the control of lymphatic filariasis (12). Some studies showed that also higher doses of ivermectin were well tolerated in adults with multiple doses up to 3 days of 600 µg/kg per day or up to a single dose of 2000 µg/kg (13–16). Currently there is evidence for a three-day course of 300 µg/kg ivermectin to be the most promising regimen for future mass drug administrations (14).

For severe crusted scabies, up to seven 200 µg/kg doses within a month in combination with topical treatment and keratolytics are recommended in the US (17) and Australia (18). The possibility of using more than 3 doses for the treatment of moderate to severe crusted scabies cases is included in the Australian product information (IPC-MK0933-T-062010) (4). Pharmacokinetic investigations of ivermectin single dose (12 mg) showed a Tmax at 4.4 hours post-dose and a half-life of 38.9 hours (31).

### 3.4. Ivermectin as additional tool in malaria control

Recently, ivermectin has emerged as a potential new additional tool for malaria transmission blocking and control (19,20) because of its capacity to inhibit parasite transmission (21–23) and sporogony (24–26), and its insecticidal activity (27–30). Personal data (publication pending) suggest that ivermectin is also active against asexual stages (Table 1) and mature gametocytes (Table 2) *in vitro*.

| Drug-sensitivity assay |                                     |              |
|------------------------|-------------------------------------|--------------|
| Parasite strains       | Drugs (IC 50 ± SD in nM) |              |
|                        | Chloroquine                         | Ivermectin   |
| 3D7                    | 3.3 ± 1.5                           | 100 ± 32.1   |
| Dd2                    | 206.9 ± 52.7                        | 110 ± 42.2   |
| JH1                    | 103 ± 20.6                          | 21.5 ± 6.9   |
| JH13                   | 111.2 ± 21                          | 126.4 ± 40.6 |

|      |              |              |
|------|--------------|--------------|
| JH26 | 10.9 ± 4.2   | 137.9 ± 38.2 |
| K1   | 321.7 ± 72.1 | 365.3 ± 92.3 |

**Table 1:** Results of the asexual growth inhibition assay for chloroquine and ivermectin presented as IC50 in nM. The assay was performed at least three times in duplicate. The mean ± standard deviation is given.

| Drug-sensitivity assay |                            |
|------------------------|----------------------------|
| Drugs                  | IC 50 ± SD (nM) |
| Chlorotoni A           | 6.43 ± 3.6                 |
| Methylene Blue         | 284.9 ± 203.4              |
| Epoxomicin             | 2.7 ± 1.7                  |
| Ivermectin             | 558.7 ± 103.9              |

**Table 2:** IC50 values in nM of different compounds against mature gametocytes of *P. falciparum*. The assay was performed in duplicate for at least three times. The mean ± the standard deviation is given.

A clinical trial in asymptomatic infected adult participants will provide valuable data regarding this potential therapeutic effect. As reference, the Cmax reached after a single dose of 400 µg/kg accompanied by a standard fatty diet is 260 ng/ml (16), this is approximately 3x the 50% inhibitory concentration for most strains. The JH strains (JH1, JH13, JH26) are clinical isolates collected in 2009 from Participants from Lambaréné, Gabon adapted to continuous culture. An IC50 value of 100 nM corresponds to 87 ng/mL, a concentration that can be kept for 12 h when an oral single dose of 30 mg of ivermectin is given with food, therefore the *in vitro* inhibitory effects could also be translated to an *in vivo* effect. One of the potential molecular explanations for the activity of ivermectin in *P. falciparum* is the inhibition of the nuclear import of signal recognition particle components (30). The results of this phase 1 proof-of-concept trial should back decisions about future ivermectin trials in Gabon.

## 4. Trial design

### 4.1. Trial overview

The study is designed as a dose escalation trial with who stapes to assess the safety and efficacy of ivermectin on the reduction of *P. falciparum* parasitaemia in asymptomatic participants in

an endemic area of Gabon. The first stage is an open label trial and included arms I-III. The next stage is a randomized double-blind controlled trial. Potential adult participants living in Lambaréné and in the Tsamba-Magotsi Department, Gabon will be screened for parasitaemia of 200 to 5000 *P. falciparum* parasites/ $\mu$ l without clinical signs of malaria for inclusion in the clinical trial. Participants will be included sequentially in arms I-IV with a pause between arms to allow safety review by DSMB. Each dose escalation stage will only commence after safety assessment of the previous stage and approval by the Data and Safety Monitoring Board. The sponsor can, in consultation with the DSMB, suspend recruitment at any time based on safety considerations.

Study arms:

- Arm I: 5 participants (200  $\mu$ g/kg single dose)
- Arm II: 5 participants (2x200  $\mu$ g/kg)
- Arm III: 5 participants (3x200  $\mu$ g/kg)
- Arm IV:
  - a) 17 participants (3x300  $\mu$ g/kg)
  - b) 17 participants (placebo-control)

All participants will be hospitalized for three days. Assessment during treatment period and follow-up visit will be the same in all study arms.

## 4.2. Objectives

### 4.2.1. Primary objective

- To assess the safety and tolerability of single- and multiple ascending doses of ivermectin in volunteers with asymptomatic *P. falciparum* infection
- To assess the efficacy of ivermectin in participants with asymptomatic *P. falciparum* infection

### 4.2.2. Secondary objectives

- To compare efficacy of ivermectin 200 $\mu$ g/kg single dose versus two-day 200 $\mu$ g/kg treatment versus three-day 200 $\mu$ g/kg treatment versus three-day 300 $\mu$ g/kg treatment
- To compare efficacy of ivermectin three-day 300 $\mu$ g/kg treatment compared to placebo
- To compare safety and tolerability of ivermectin 200 $\mu$ g/kg single dose versus two-day 200 $\mu$ g/kg treatment versus three-day 200 $\mu$ g/kg treatment versus three-day 300 $\mu$ g/kg treatment
- To compare safety and tolerability of ivermectin three-day 300 $\mu$ g/kg treatment compared to placebo

#### 4.2.3. Exploratory objectives

- To assess effect of pharmacokinetic parameters on efficacy and safety
- To assess activity of ivermectin on *P. falciparum* gametocytes
- To assess parasite kinetics in the placebo group
- To assess the mosquitocidal effect
- To assess the effect on the metabolome. As ivermectin has an influence on the worm burden stool sample analysis will enable to relate this to metabolomic changes.

## 5. Study population

### 5.1. Sample size

Treatment Arms I-III serves to cautiously assess the safety of Ivermectin against *Plasmodium falciparum* infections and the sample size for these treatment arms is purely descriptive.

As in Arm IV the currently envisaged dose for ivermectin mass drug administrations in malaria elimination programs will be assessed, this arm has a formal sample size and placebo-controls. To calculate the sample size, we considered the time to 90% parasite reduction of the participants in the 3-day treatment group versus the time to 90% parasite reduction in the placebo group. Based on previous data, we assume that 25% of volunteers allocated to placebo will reduce parasitaemia to 90% of the initial value within 7 days and expect that at least 75% of ivermectin-treated volunteers will reach the endpoint. With a power of 90%, a single-sided alpha of 2.5% and a ratio 1:1 (treatment versus placebo group), 17 events (achieving 90% parasite reduction) are required (32). Consequently, 17 volunteers will be recruited per arm. Therefore, a total of 49 evaluable participants is required. Participants who are lost to follow up will be included in the safety analysis, but replacements will be recruited to reach the number of 49 evaluable participants.

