### **5.5. Withdrawal of Participants**

In accordance with the principles of the current revision of the Declaration of Helsinki (updated 2013) and any other applicable regulations, a participant has the right to withdraw from the study at any time and for any reason and is not obliged to give his or her reasons for doing so. The Investigator may withdraw the participant at any time in the interests of the participant's health and well-being. In addition, the participant may withdraw/be withdrawn for any of the following reasons:

- Investigator decision
- An AE, which requires discontinuation of the study involvement or results in inability to continue to comply with study procedures

The reason for withdrawal will be recorded in the CRF. If withdrawal is due to an AE, appropriate follow-up visits or medical care will be arranged, with the agreement of the participant, until the AE has resolved, stabilized or a non-trial related causality has been assigned. Any participant who is withdrawn from the study may be replaced, if that is possible within the specified time frame.

If a participant withdraws from the study, blood samples collected before their withdrawal from the trial will be used/ stored unless the participant specifically requests otherwise. The samples may be destroyed if the participant did not agree to have their samples stored.

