#### 6.2.2. Randomization of treatment

As Arms I-III serves descriptive purposes for safety assessment of the study drug, there will be no randomization.

Participants for Arm IV will be randomized to arm IVa or arm IV b through a randomization system prior to the first treatment. The randomization ratio will be 1:1 (3-day treatment, control group). A dedicated member of the team, who is not involved in volunteer management or diagnostic activities, will keep the randomization envelopes and dosing schedule. A third party outside the study team and sponsor will generate and distribute the randomization list and sealed envelopes using a random number generator.

A sealed envelope containing the participants arm will be used for randomization in the study and the randomization data are kept strictly confidential until formal interim safety review or the final analysis. At the time of final analysis, the allocation data will be loaded into the statistical programming system for access to trial statisticians and pharmacokinetics.

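### The replacement rule in 5.1 and 5.5 has no exemption for randomised Arm IV and can be read as substituting lost participants in the efficacy comparison

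*Protocol*

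**What the plan says.** Protocol 5.1 derives 17 events and 17 volunteers per arm for Arm IV. It adds Arms I-III to reach 49 evaluable participants (5 + 5 + 5 + 17 + 17). On losses it says: "Participants who are lost to follow up will be included in the safety analysis, but replacements will be recruited to reach the number" of 49. It does not define *evaluable* and makes no exception for the 34 randomised participants.

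Section 5.5 adds: "Any participant who is withdrawn from the study may be replaced, if that is possible within the specified time frame". Its listed reasons for withdrawal include an adverse event and investigator decision.

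Section 6.2.2 describes sealed-envelope allocation in Arm IV but does not say how a replacement is allocated. The protocol has no statement that efficacy is analysed as randomised. The primary efficacy endpoint (8.1) is a time to event: 90% parasite reduction, held for at least 8 hours, by microscopy.

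**The concern.** Arm IV is the only randomised and the only formally sized comparison. A person who must be replaced to reach the evaluable number is, on the natural reading, not counted as evaluable. Section 5.1 names the safety analysis as the place where such people are kept. Followed that way, the efficacy comparison would consist of those who stayed plus substitutes, and no longer of the groups formed by randomisation.

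Loss after dosing may depend on treatment (for example through adverse events) and on outcome. If it depends on both, replacement changes one arm's response rate. With about 17 events in total there is little room to absorb this. A time-to-event endpoint does not need the rule, because a lost participant can contribute up to the last film.

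**Working it through.** **1. The plan's own figure.** Inputs from 5.1 and 6.2.2:
- "With a power of 90%, a single-sided alpha of 2.5% and a ratio 1:1 (treatment versus placebo group");
- "we assume that 25% of volunteers allocated to placebo will reduce parasitaemia to 90% of the initial value within 7 days", taken here to mean a reduction by 90%;
- "expect that at least 75% of ivermectin-treated volunteers will reach the endpoint";
- "The randomization ratio will be 1:1 (3-day treatment, control group").

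Hazard ratio = ln(1 − 0.75) / ln(1 − 0.25) = 4.82, and its logarithm is 1.5725. Schoenfeld events = 4 × (1.960 + 1.2816)² / 1.5725² = 16.996, so 17. This agrees with "17 events (achieving 90% parasite reduction) are required (32"). Expected events with 17 per arm are 17 × (0.25 + 0.75) = 17. The sample size arithmetic reproduces and is not at issue.

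**2. What replacement does to the apparent response.** Let p be the true 7-day response and r the share of non-responders lost and replaced. The apparent response is p / (p + (1 − p)(1 − r)).

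| p | r | share of that arm lost, (1 − p) × r | apparent response |
|---|---|---|---|
| 25% | 20% | 15% | 0.25 / 0.85 = 29% |
| 25% | 30% | 22.5% | 0.25 / 0.775 = 32% |
| 75% | 20% | 5% | 0.75 / 0.95 = 79% |
| 75% | 30% | 7.5% | 0.75 / 0.925 = 81% |

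At p = 25%, filling 17 places takes about 17 × 0.15 / 0.85 = 3 or 17 × 0.225 / 0.775 = 5 replacements, all in one arm.

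**3. Type I error, worst case.** Simulated log-rank test, 17 per arm, constant hazards, the protocol's film times (8-hourly to H72, then daily to Day 7), one-sided 2.5%, no true effect. Only ivermectin non-responders are lost, and each is replaced.

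| r | response 25% | response 50% |
|---|---|---|
| 0 | 2.4% | 2.6% |
| 20% | 4.7% | 5.1% |
| 30% | 6.7% | 7.3% |
| 40% | 9.7% | 10.9% |

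At 25% response, exactly one or two such substitutions give only about 3.1% or 4.0%.

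**4. Other patterns of loss.** A second simulation (40,000 runs, 25% response under the null) placed losses after Day 3 among participants who had not yet responded.

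| Loss | replaced | all kept, censored |
|---|---|---|
| none | 2.4% | 2.5% |
| 16% of both arms | 2.4% | 2.5% |
| 16% of ivermectin only | 4.1% | 2.5% |
| 33% of ivermectin only | 7.6% | 2.6% |
| 33% of placebo only | 0.6% | 2.3% |

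With a true 75% against 25%, replacement after placebo-side loss at the same setting cuts simulated power from 0.88 to 0.72.

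In this simulation the lost had the same prospects as others still without a response, which is the condition under which censoring is valid. If the lost would never have responded, censoring removes most of the bias but not all of it.

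**5. Cost of keeping everyone.** If events fall in proportion to loss, 10% loss leaves 15.3 events. Power is then Φ(√15.3 / 2 × 1.5725 − 1.960) = 86.8%. At 5% loss it is 88.5% and at 20% it is 82.6%. Randomising 17 / 0.9 = 18.9, so 19, per arm covers 10% loss. The protocol gives no loss rate, so all loss rates here are assumptions.

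**The case against.** The exclusion from efficacy is inferred. Section 5.1 says that lost participants are included in the safety analysis; it does not say only there. *Evaluable* appears undefined in a sample size paragraph, and a statistical analysis plan, not at hand, may keep everyone randomised. This stands, and is why the point is worded as a natural reading. It does not dispose of the point: the replacement instruction is in the protocol itself, covers Arm IV, and would conflict with an as-randomised analysis unless reconciled.

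The design also makes heavy, one-sided loss unlikely. Participants are in hospital for at least 72 hours, which covers all dosing, and are seen daily to Day 7 (section 9). Costs are reimbursed (section 11) and allocation is blinded (6.2.3). Participants are asymptomatic, so they would not feel a failure of parasites to fall. Missed visits should not lead to automatic discontinuation (7.2). Rescue medication is not listed in 5.5 as a reason for withdrawal. This stands and limits the likely size.

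A reader might also infer that a replacement must go to the lost participant's arm and so reveals that arm. The documents do not support this. Section 5.1 fixes a total, and no allocation rule for replacements is given. Sections 6.2.2 and 6.2.3 keep the envelopes away from those managing volunteers and reading films. Even a same-arm replacement would tell blinded staff only that two people share an arm, not which arm it is.

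**Conclusion.** The concern holds as a rule that can be read to replace randomised participants in the efficacy comparison, and it should be fixed. It is not shown that efficacy will be so restricted, nor that a false ivermectin effect will follow.

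The bias needs loss that differs by arm and is related to outcome. In the assumed worst case, with 15% or 22.5% of the ivermectin arm lost, all of them non-responders, and none on placebo, one-sided type I error is about 4.7% or 6.7% in place of 2.5%. Equal loss leaves it near 2.5%, and placebo-side loss biases against ivermectin and lowers power.

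A reader might conclude that one or two substitutions are enough to overturn the result. At the protocol's 25% response they take type I error only to about 3% or 4%. Replacement in the non-randomised Arms I-III does not raise this problem.

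**What to change.** In 5.1 and 5.5, limit replacement to Arms I-III or, in Arm IV, to participants who leave before randomisation. Then add for Arm IV:

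- The primary efficacy analysis includes every participant randomised in Arm IV, as randomised, censored at the last film if lost.
- A sensitivity analysis counts lost participants as non-responders. It is not a bound in both directions: in the second simulation, with 33% placebo-only loss, it gave a type I error of 3.7%, so it is read beside the censored analysis.
- Any additional Arm IV participant takes the next sealed envelope, and the original participant stays in the analysis.

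The cost is a few sentences and a small loss of power if participants are lost: about 87% at an assumed 10% loss, or 19 randomised per arm to hold 90%. A participant lost on Day 4 already has nine post-dose films (H8 to H72), so little information is given up. No dose, schedule or clinical rule changes.

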### 5.2. Inclusion criteria

Participants eligible for inclusion in this study must fulfil all of the following criteria:

- Male or female, aged  $\geq 18$  years and body weight  $\geq 45$  kg
- *P. falciparum* parasitaemia of 200 to 5000 parasites/ $\mu$ L
- Asymptomatic *P. falciparum* infection defined as: presence of *P. falciparum* mono-infection with absence of fever (axillary temperature  $<38.5$  °C and absence of history of fever in recent 24 hours and the week before inclusion) and other symptoms related to malaria.

- Willingness to take part in the study and to sign the informed consent form

